##### Nested qualitative study

The nested qualitative study protocol is included in Supplementary File 3 and analysis is briefly outlined here. We will conduct telephone interviews at baseline, and at 6 and 12 months follow up among a sub-sample of patients and clinicians to allow qualitative evaluation of the intervention. We will invite participants who were randomised to both the intervention and control arms (controls at 12 months only) who indicated their interest in taking part in an interview to explore, in-depth, their experiences in the trial. A longitudinal format will be applied to interviews with intervention arm participants (see Supplementary File 3). Participants who withdraw from the intervention group will be approached for an interview also. Interviews will be audio-recorded and transcribed verbatim. Interviews with clinicians (*n* = 5–10) will explore their experience of the benefits and limitations of the intervention. The study will take a phenomenological perspective and will use Framework Analysis [53], a matrix-based method of thematic analysis which has been used successfully in other studies of early detection technologies [54, 55].

##### Dermatoscope technology comparison sub-study

We will compare performance of the two models of mobile dermatoscope (cross-polarised light dermatoscope or natural light dermatoscope) on the following outcomes:
Quality of image as reported by teledermatologists.Adherence measured by the proportion of participants who have an image reported on at each of the 3 monthly submission points.Participant satisfaction.Protocol deviations, adverse events and device deficiencies related to use of the dermatoscope, app or teledermatology platform (for example, dermatoscope breakage, incorrect storage or transmission of images, delayed transmission of images).

We will measure these outcomes throughout the active trial period and analyse them using an appropriate statistical model that allows for repeated measures. The combination of adherence with the technology and quality of images will also be used for adaptive randomisation to protect against poor performance of one dermatoscope (see section 16).

### Interim analyses {21b}

Interim analyses will be conducted by an independent statistician after 33% of trial participants (approximately 200) have been recruited and, following this, after every 6 months. The interim analyses will be done masked to randomised groups and will estimate the frequency of the primary outcome to assess assumptions made for the sample size calculations, as well as the number of participants recruited, withdrawals and adverse events. Separate to the interim analyses described above, there will be an analysis as part of the adaptive randomisation after 60 participants have been randomised to the intervention arm (as described in Section 16). This will be limited to analysis of the device-related outcomes in the intervention arm only. There will be no comparison to the control group or estimation of effect on the primary outcome or other secondary outcomes for the adaptive randomisation. Any changes in the ratio of randomisation between the two types of device as a result of the adaptive randomisation will also be presented to the Data Safety Monitoring Committee (DSMC).

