#### Composition of the data monitoring committee, its role and reporting structure {21a}

The Data Safety Monitoring Committee (DSMC) will comprise three trial methodologists (senior statistician(s) and clinical trialist(s)) who are independent of the study team. The DSMC will meet to review each interim analysis and decide on any actions needed, which will be communicated to the Trial Management Committee.

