#### Adverse event reporting and harms {22}

Please see Supplementary file 4.

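### The interim adverse-event data reviewed by the DSMC are masked to randomised group, and the protocol article describes no by-arm safety report

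*Protocol article*

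**What the plan says.** Section {21b} of the protocol article sets the interim analyses "after 33% of trial participants (approximately 200) have been recruited and, following this, after every 6 months". On who performs them it says: "Interim analyses will be conducted by an independent statistician". On masking: "The interim analyses will be done masked to randomised groups". Their content is the frequency of the primary outcome, to check the sample-size assumptions, "as well as the number of participants recruited, withdrawals and adverse events".

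Section {21a} describes a committee of three methodologists "who are independent of the study team" and gives it this task: "The DSMC will meet to review each interim analysis and decide on any actions needed".

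The same section {21b} sets out a separate analysis for the adaptive device randomisation, of which it says: "This will be limited to analysis of the device-related outcomes in the intervention arm only".

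The harms section {22} consists of one referral: "Please see Supplementary file 4". Section {25} also names a data safety management plan among the ethics-approved documents. Neither document is shown.

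**The concern.** Masking the primary-outcome frequency has a clear purpose: it lets the sample-size assumptions be checked without revealing a treatment effect. Section {21b} applies the same mask to withdrawals and adverse events and gives no reason for doing so. The trial is open label apart from outcome assessment ({17a}, {17b}), the committee is independent, and so is the statistician who prepares its report. Masking the safety data from that committee therefore protects little.

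The intervention is added to usual care ({6b}, {11a}), so any harm it causes, such as distress from repeated self-examination or additional excisions, would fall in one arm. The protocol itself treats severe DASS-21 scores as a safety matter ({30}) and counts lesions surgically evaluated (outcome M8). A committee that must decide on action from data without allocation may be unable to judge whether a high count reflects the intervention or the background rate in this population.

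**Working it through.** **1. The safety provisions the article does show**

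| Section | Provision | Compares arms? |
|---|---|---|
| {21b}, interim analyses | Adverse events and withdrawals, masked to group | No, if pooled; without direction, if coded |
| {21b}, adaptive analysis | Device outcomes, intervention arm only | No |
| {23} | Adverse event reporting rates between sites | No |
| {30} | Contact with individuals above the severe DASS-21 threshold | No |
| Dermatoscope sub-study | Adverse events and deficiencies tied to device, app or platform | No, device vs device |

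**2. The plan's own figure**

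The primary sample size in {14} assumes 1% vs 6%, two-sided 5%, Fisher's exact test. Summing the exact binomial probabilities of all tables with Fisher p ≤ 0.05 gives power 0.799 at 225 per arm and 0.801 at 226, so the stated 226 per arm reproduces. Allowing for 25% dropout, 452 / 0.75 = 603, against 600 planned. A by-arm safety table changes none of this.

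**3. What a pooled count hides**

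Take 200 participants, 100 per arm under 1:1 allocation, and assume 12 have an adverse event. The pooled rate is 12 / 200 = 6% for every split.

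| Split | Pooled rate | Fisher p by arm |
|---|---|---|
| 6 vs 6 | 6% | 1.00 |
| 3 vs 9 | 6% | 0.13 |
| 2 vs 10 | 6% | 0.033 |
| 1 vs 11 | 6% | 0.005 |
| 0 vs 12 | 6% | 0.0003 |

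Under coded groups the committee would see 0 vs 12, but not which arm had the 12.

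**4. How much a by-arm table could detect, using DASS-21 as the example**

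Follow-up DASS-21 is collected only at 6 and 12 months ({13}, {18a}), so participants count only once they have been in the trial for 6 months. Assume even recruitment of 600 over the 2 years in {15}: 600 / 24 = 25 a month.

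- First look: 200 / 25 = month 8. Those with 6-month data entered in the first 8 − 6 = 2 months: 2 × 25 = 50, or 25 per arm.
- Second look: month 8 + 6 = 14. Those with 6-month data entered in the first 14 − 6 = 8 months: 8 × 25 = 200, or 100 per arm. By then 14 × 25 = 350 are recruited, or 175 per arm.

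The statistic is z = (p₂ − p₁) / √[2p̄(1 − p̄)/n], where p₁ and p₂ are the observed proportions, p̄ is their mean and n is the number per arm. The test rejects if |z| ≥ 1.96. Power is the exact binomial probability of rejection. The event rates are assumptions; the documents give none.

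| Per arm | 5% vs 15%: z-test | 5% vs 15%: Fisher | 5% vs 10%: z-test | 5% vs 10%: Fisher |
|---|---|---|---|---|
| 25 (first look) | 0.21 | 0.07 | 0.08 | 0.01 |
| 100 (second look) | 0.68 | 0.59 | 0.27 | 0.19 |

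These are before dropout, for which {14} allows up to 25%.

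**The case against.** The strongest objection is that the article is not the whole safety plan. By-arm tables for a monitoring committee usually sit in a charter or safety plan, and the article refers harms to Supplementary file 4 and names a data safety management plan. A reader might infer from {21b} that the masked review is the only interim safety review planned. The documents do not support that, because neither file is shown. What stands is that {21b} is a stated rule and not a silence. If those files do provide review by arm, {21b} conflicts with them and needs reconciling.

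Second, masked need not mean pooled. A reader might infer that the DSMC cannot see any imbalance, but {21b} does not say that the groups are combined, and coded groups would fit its wording. The ambiguity remains, and under either meaning the committee does not learn which arm is affected.

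Third, a reader might infer that harm from the intervention could surface only after the trial ends. That goes too far. Participants, site staff and treating clinicians know the allocation, severe DASS-21 scores prompt individual contact, device-related events are recorded throughout, and {11b} allows the intervention to be modified or discontinued for harm. These are routes for individual cases to be noticed. They do not compare rates between arms.

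Fourth, early by-arm data would be thin. This is correct. It would be wrong to credit the first two looks with 100 and 175 per arm for DASS-21, since most of those recruited would not yet have reached 6 months.

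**Conclusion.** The concern holds in a limited form. As written, the protocol article masks to randomised group the adverse-event and withdrawal data on which the independent DSMC is to act, does not say whether that means pooled or coded, and describes no safety comparison between arms. If pooled, an excess in one arm cannot be told from a high background rate; if coded, its direction is hidden.

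The conclusion about pooling does not depend on power. The count of 12 events is only an illustration. The gain at early looks is modest: for an assumed 5% vs 15% on DASS-21, about 21% and then 68% power by the uncorrected two-proportion test. For 5% vs 10% it is about 8% and 27%. Both rest on even recruitment, 1:1 allocation and complete 6-month data. The point does not affect the validity of the primary analysis. It is a worthwhile and inexpensive improvement to safety oversight.

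**What to change.** In {21b}, separate the two purposes of the interim analyses:

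- Keep the primary-outcome frequency pooled.
- State that the independent statistician gives the DSMC a confidential closed safety report by coded arm, with the code available to the committee on request. It should cover adverse events, withdrawals, severe DASS-21 scores and lesions excised.
- State that the Trial Management Committee and the sites do not receive this report.
- Reconcile the wording with {21a}, {22} and Supplementary file 4. If by-arm review is already provided there, a cross-reference and a corrected masking sentence are enough.

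The cost is a sentence or two of text, one extra table from a statistician already engaged, and keeping that table confidential. No efficacy comparison is added, so no alpha is spent and the 452 evaluable and 600 recruited are unchanged.

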### Methods for additional analyses (e.g. subgroup analyses) {20b}

Subgroup analyses will be conducted to assess whether the effect of the intervention on the primary outcome (patient-led vs clinician-led surveillance) differs across the following patient characteristics (interaction between randomisation variable and patient characteristic):
AJCC melanoma substageRisk of a subsequent new primary melanoma (1-year risk, continuous variable [48])Dysplastic naevus syndrome (yes or no)Age (continuous variable)Confidence in digital technology/digital health literacy

### Methods in analysis to handle protocol non-adherence and any statistical methods to handle missing data {20c}

Missing data will be accounted for by sensitivity analyses. Each variable will be assessed for missing data and if more than 10% of the data are observed to be missing on key variables, sensitivity analyses will be performed using an appropriate analysis method, such as multiple imputation, instrumental variable analysis or inverse probability weighting [56]. In addition, a per-protocol analysis will be conducted on the primary outcome to estimate the effect that would have been observed had all participants adhered to the protocol.

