### Sample size {14}

Assuming that 6–8% of patients in the clinician-led surveillance group have a subsequent new primary or recurrent melanoma diagnosed within the 12 months follow up [21, 45] and that 1% have a diagnosis through a fast-tracked unscheduled clinic visit, we will need to recruit at least 452 participants (226 to patient-led surveillance and 226 to clinician-led surveillance) in order to have at least 80% power to detect a 5% absolute increase in the patient-led surveillance group (i.e. 6% have new or recurrent melanoma diagnosed through unscheduled visit at treatment centre). Assuming up to 25% of study participants withdraw consent or dropout, we will recruit 600 participants (300 to patient-led surveillance and 300 to clinician-led surveillance). These calculations assume a two-sided 5% significance level and were done using Fisher’s exact test. This sample size will also ensure at least 80% power to detect a hazard ratio of 1.71 for time from randomisation to diagnosis of a skin cancer for the patient-led vs clinician-led surveillance groups (due to earlier and increased detection in the patient-led group). This calculation assumes a 20% event rate in the clinician-led surveillance group [21, 45] (60 events among 300 control participants), a 32% event rate in the patient-led surveillance group (96 events among 300 intervention participants), and 26% event rate overall (156 events among 600 trial participants).

For the nested qualitative study, we will aim to recruit 30–45 participants, which may vary depending on the saturation of themes but is a sample size commonly sufficient to reach saturation in themes and topics [46].

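### The more-than-10% trigger for missing-data sensitivity analyses is too coarse for a primary outcome expected in about 3.5% of participants

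*Protocol article*

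**What the plan says.** The section on missing data ({20c}) opens with a general statement, "Missing data will be accounted for by sensitivity analyses", and then sets a condition: "if more than 10% of the data are observed to be missing on key variables, sensitivity analyses will be performed". The methods are given as examples, "such as multiple imputation, instrumental variable analysis or inverse probability weighting". The same cut-off applies to every key variable, and the primary outcome has no rule of its own.

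The sample size section ({14}) assumes that in the control arm "1% have a diagnosis through a fast-tracked unscheduled clinic visit" and that in the intervention arm "6% have new or recurrent melanoma diagnosed through unscheduled visit at treatment centre". It puts melanoma found by any route in the control arm at 6–8% over 12 months. It allows for losses: "Assuming up to 25% of study participants withdraw consent or dropout".

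Three other places bear on how much primary-outcome data will be missing:
- Study staff review medical records, and trial data are linked to site databases, the state cancer registry and Medicare claims (data collection {18a}, pathology and linkage).
- After withdrawing from active follow-up, participants may agree to continued passive data collection. Those who move out of the state can be withdrawn (retention {18b}).
- A committee classifies each visit as scheduled or unscheduled from the participant's clinic letters (primary outcome {12}).

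**The concern.** A percentage trigger ignores how common the outcome is. For a questionnaire score, 10% missing is a modest share of the information. For a binary outcome with a pooled rate of 3.5%, 10% missing is nearly three times the number of expected events, so the participants who are not observed could hold more events than the trial expects to count. A significant result could then depend on a few unseen control diagnoses, and the stated rule would not require anyone to look. The trial's main claim rests on this one comparison of small counts.

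**Working it through.** **Inputs.** From the sample size section: rates of 1% and 6%, 300 per arm, two-sided 5%, Fisher's exact test. From {20c}: trigger at more than 10% missing. Assumed here, because the protocol gives no figure: 9% of primary outcomes missing, equally in both arms, and a main analysis of those observed. Fisher's test stands in for the planned generalised linear model.

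**The plan's own figure.** Exact Fisher power for 1% versus 6% is 0.799 at 225 per arm and 0.801 at 226, so the stated 226 per arm (452 in total) is reproduced.

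**Trigger against event count.**
- Pooled rate: (1% + 6%) / 2 = 3.5%; 10 / 3.5 = 2.86.
- Expected events: 300 × 0.01 = 3 and 300 × 0.06 = 18, so 21 in total and a difference of 15.
- Largest number missing without firing the trigger: 600 × 0.10 = 60, which is 60 / 15 = 4 times the planned difference.

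**Tipping point at 9% missing.**
- Missing per arm: 300 × 0.09 = 27, leaving 273 observed.
- Expected observed events: 273 × 0.01 = 2.7, taken as 3; 273 × 0.06 = 16.4, taken as 16. Fisher p = 0.0038.
- Add k events among the 27 missing controls and analyse 300 per arm:

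| k | No events in missing intervention participants (16/300) | Two events in missing intervention participants (18/300) |
|---|---|---|
| 2 | 5 vs 16, p = 0.024 | 5 vs 18, p = 0.009 |
| 3 | 6 vs 16, p = 0.048 | 6 vs 18, p = 0.020 |
| 4 | 7 vs 16, p = 0.087 | 7 vs 18, p = 0.039 |
| 5 | 8 vs 16, p = 0.143 | 8 vs 18, p = 0.069 |

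Two events is the expected number among 27 participants at the intervention rate (27 × 0.06 = 1.6). Missing controls at that rate, with no events in the missing intervention participants, leave the result significant (p = 0.024). In the same column, equal counts need k = 13 and a change of direction needs k = 14 or more.

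**Across possible trials.** The table takes the expected result; many significant trials will be closer to the boundary. Enumerating all significant results at 1% versus 6% with 273 observed per arm, and adding hidden control events only, significance is lost in 20% of them with 2 such events and in 49% with 4.

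**The case against.** The strongest reply has four parts.

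- **The analysis plan is separate.** The protocol defers missing-data methods to it, and the methods in {20c} are only examples. This stands as far as methods go: the absence of a tipping-point analysis from that list is not a fault in itself, and a reader should not infer that such an analysis is ruled out. But the 10% trigger is stated in the protocol, and the unconditional opening sentence is narrowed by the one after it.
- **The primary outcome needs little participant contact.** It comes from histology, clinic letters, record review and linkage, all already planned, so missingness may be well under 9%. This largely stands. It does not remove the gap, because passive collection after withdrawal depends on consent, and a melanoma found through the registry still needs a clinic letter before the visit can be classified.
- **The scenarios are one-sided.** Four events in 27 controls is 15%, against a design rate of 1%. The binomial probability of 4 or more is 0.0001 at 1%, 0.08 at 6% and 0.17 at 8%; the last two require every melanoma in the missing controls to have been found at an unscheduled visit. This stands as a limit on likelihood.
- **The 25% dropout allowance would fire the trigger** if it became missing primary data. This is correct, so that allowance does not strengthen the point.

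A reader might also infer that loss must differ by arm because only the intervention arm has devices and image tasks. The documents do not establish this: questionnaires, resource diaries and retention reminders apply to both arms. The direction of any imbalance is unknown.

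**Conclusion.** The point holds in a limited form. The protocol fixes a uniform trigger that lets up to 60 primary outcomes go missing without any required sensitivity analysis, in a trial expecting about 21 events. At an assumed 9% missing, the expected significant result is lost with 4 hidden control events, or 5 if the missing intervention participants have their expected 2. It survives the milder case of missing controls at the intervention rate.

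A reader might go further and infer that missing data within the trigger could reverse the finding. That would take 14 or more events among the missing controls with none in the intervention arm, which the stated rates make implausible. The realistic risk is loss of significance, and only where missingness is 10% or less. The size rests on the design rates, the assumed level and equal split of missingness, and Fisher's test as a stand-in for the planned model. The rule should be changed, but it does not undermine the design.

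**What to change.** Remove the 10% trigger for the primary outcome. First fill outcomes from the record review and consented linkage already planned. Then, whatever the level of missingness:

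1. Report the number and proportion with a missing primary outcome by arm, separating an unknown diagnosis from a known melanoma whose visit cannot be classified.
2. Run a tipping-point analysis in which the assumed event rate among the missing varies separately in each arm, including missing controls at the observed intervention rate, and show where significance is lost.

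The percentage trigger may stay for questionnaire outcomes. The cost is a short wording change in the protocol and analysis plan and one extra results table; no additional data collection or sample size is needed.

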### Plans to give access to the full protocol, participant level-data and statistical code {31c}

Non-identifiable data and statistical code will be made available to other approved researchers to maximise the benefits that can be derived from the data. Access to NSW Cancer Registry (NSWCR) data requires the approval of the NSWCR Data Custodian. Access to the full protocol and to data (other than NSWCR data) may be requested via the CPI, Associate [name].

### Oversight and monitoring

#### Composition of the coordinating centre and trial management committee {5d}

The Trial Management Committee (TMC) will coordinate the conduct of the trial and is independent of the trial’s financial sponsorship. TMC members include KB, MJ, AC, RT, LI, PG, RS, RPMS, VM, MD, JH, RM, Cl, DL, JT, JE and RAS. TMC responsibilities include protocol development; study planning, monitoring and progress; review of information from related research; and implementation of recommendations from other study committees and external bodies (e.g. Human Research Ethics Committee). The Expert Clinician Reference Group includes medical practitioners who have specific clinical roles in the trial (e.g. teledermatologists, treating doctors, pathologists), contributed to protocol development and provide ongoing clinical advice. The Trial Coordinating Team (TCT) consists of project coordinators, data managers and research assistants and is led by the Coordinating Principal Investigator (CPI). The TCT is responsible for the day-to-day management and governance of the trial.

